***Note: ORR=* sCR *+* CR *+* VGPR *+* PR *+* MR**

## Lymphoma Efficacy Evaluation Criteria

* For B-cell lymphoma and T-cell lymphoma, refer to the following criteria.

**International Working Group (IWG) Lymphoma Response Evaluation Criteria (2017)**

|  | **Complete Response（CR）** | **Partial Response（PR）** | **Minor Response（MR）** | **Stable Disease（SD）** | **Progressive Disease（PD）** |
| --- | --- | --- | --- | --- | --- |
| Change from baseline (%) | All target lesions completely disappear, and the longest diameter of all lymph nodes is < 10 mm; | The sum of the longest diameters of target lesions decreases by ≥30% (Partial Response), but does not reach Complete Response; | The sum of the longest diameters of target lesions decreases by ≥10%, but does not reach Partial Response; | The sum of the longest diameters of target lesions decreases by <10% or increases by ≤20%; | The sum of the longest diameters of target lesions increases by >20% |
|  | The sum of the longest diameters of target lesions decreases by ≥30% (Partial Response), while the FDG-PET scan results are normal; |  |  |  |  |
| FDG-PET CT | FDG-PET CT scan results are normal (Deauville score 1 to 3) | FDG-PET CT scan results are positive (Deauville score 4 to 5); | Any FDG-PET CT scan results | Any FDG-PET CT scan results | Any FDG-PET CT scan results |
| Bone marrow involvement | No bone marrow involvement; | Any lesions involving the bone marrow; | Any lesions involving the bone marrow; | Any lesions involving the bone marrow; | Any lesions involving the bone marrow; |
| New lesions | No new lesions. | No new lesions. | No new lesions. | No new lesions. | With or without new lesions. |

*Note: FDG-PET: 18F-fluorodeoxyglucose positron emission tomography.*

Note: ORR =CR+PR+MR; DCR= CR+PR+MR+SD

Reference: Younes A, Hilden P, Coiffier B, et al. International Working Group consensus response evaluation criteria in lymphoma (RECIL 2017) [J]. Annals of Oncology, 2017, 28(7): 1436-1447.

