## Definition of the Trial Population

The specific definition of relapsed or refractory hematologic malignancies primarily involving B-cell-related tumors is referenced as follows. For diseases not specifically defined in this section, the investigator will determine them according to the latest guidelines for each condition:

- 1. **B-cell lymphoma and T-cell lymphoma**

According to the "Guidelines for the Diagnosis and Treatment of Diffuse Large B-Cell Lymphoma in China (2013 Edition)" and recent clinical studies of newly marketed drugs, relapsedor refractory B-cell lymphoma and T-cell lymphoma are defined as follows (may not apply to certain rare or currently non-research hotspot pathological types):

- RelapsedB-cell lymphoma and T-cell lymphoma: Refers to disease progression after adequate treatment achieving remission (including PR and CR).

Disease progression is indicated by the appearance of any new lesions or an increase in the diameter of existing lesions by ≥ 50%, including but not limited to the following situations: (1) Lymphadenopathy: The appearance of any new lesion with a diameter > 1.5 cm; an increase of ≥ 50% in the sum of the products of the maximum vertical diameters of multiple lesions; or an increase of ≥ 50% in the maximum diameter of a single lesion with a short axis > 1 cm before treatment. Additionally, lesions that were FDG avid or PET positive before treatment and are PET positive after treatment. (2) Spleen and liver: An increase of ≥50% in the sum of the products of the maximum vertical diameters of any lesions. (3) New or relapsedbone marrow involvement.

- Refractory B-cell lymphoma and T-cell lymphoma: Defined as meeting any of the following criteria: (1) Disease progression after two cycles of standard regimen chemotherapy, or failure to achieve remission (including PR and CR) after four cycles of treatment; (2) Achieving CR after standard regimen chemotherapy, followed by relapse within 6 months; (3) Two or more relapses after achieving CR; (4) Relapse after hematopoietic stem cell transplantation.
  1. **B-cell acute leukemia and T-cell acute leukemia (collectively referred to as acute lymphoblastic leukemia, ALL)**

According to the "Guidelines for the Diagnosis and Treatment of Adult Acute Lymphoblastic Leukemia in China (2016 Edition)" and the National Comprehensive Cancer Network (NCCN) guidelines, relapsedor refractory acute lymphoblastic leukemia in adults is defined as follows:

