## Efficacy Evaluation

- Objective Response Rate (ORR): Defined as the proportion of patients whose tumor volume has decreased to a predetermined value and maintained for a minimum required duration. ORR is generally defined as the sum of complete response (CR) and partial response (PR).
- Progression-Free Survival (PFS): The time from the start of patient enrollment until the occurrence of objective tumor progression or death.
- Disease Control Rate (DCR): Refers to the proportion of patients whose tumors have either decreased or stabilized for a certain period, including cases of complete response (CR), partial response (PR), and stable disease (SD).

The efficacy evaluation correspondence for this trial is referenced in the table below. For other diseases not specified in the table, the investigator will determine efficacy based on the latest evaluation criteria for that disease:

| Disease Names | Efficacy Evaluation Criteria |
| --- | --- |
| B-cell Lymphoma  T-cell Lymphoma | ORR =CR+PR+MR  DCR= CR+PR+MR+SD |
| Multiple Myeloma | ORR =sCR+CR+VGPR+PR+MR |
| B-cell Acute Lymphoblastic Leukemia  T-cell Acute Lymphoblastic Leukemia | ORR= CR+CRi  This disease is not applicable for DCR analysis. |
| Other Relapsed or Refractory Hematologic Malignancies | For diseases not defined in this trial, the determination will be based on the clinical researcher's judgment according to the efficacy evaluation guidelines for each disease. |

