| **PD** | Meets any one or more of the following criteria:  Any one or more of the following criteria indicate a minimum confirmation of response value increase of 25%.   - Serum M protein (the absolute increase must be > 0.5 g/dL); - If the baseline minimum M component value is ≥5 g/dL, an increase in serum M protein of ≥1 g/dL; - Urine M protein (the absolute increase must be ≥200 mg/24 h); - For patients where serum and urine M protein levels cannot be measured, the difference in free light chain (FLC) levels between the affected and unaffected areas (the absolute increase must be >10 mg/dL); - For patients where serum and urine M protein levels cannot be measured and where the FLC levels in the affected area cannot be measured, the percentage of plasma cells in the bone marrow is not affected by baseline status (the absolute increase must be ≥10%); - New lesions appear, with the SPD of >1 lesion increasing by ≥50% from the lowest value, or the maximum diameter of the original lesion with a minimum diameter >1 cm increasing by ≥50%; if this is the only measurable value of the disease, the number of circulating plasma cells (at least 200 cells per μL) increases by ≥50%. |
| **Clinical relapse** | Clinical relapse requires one or more of the following criteria:   - Direct indicators of disease progression and/or end-organ dysfunction (such as elevated calcium levels, renal failure, anemia, and osteolytic lesions [CRAB symptoms]) associated with potential clonal plasma cell proliferation. This is not used to calculate time to progression or progression-free survival but can be selectively reported or used in clinical practice; - The occurrence of new soft tissue plasmacytomas or bone lesions (osteoporotic fractures do not constitute lesions); - A clear increase in the size of existing plasmacytomas or bone lesions. A clear increase is defined as a ≥50% increase in the SPD of measurable lesions (and ≥1 cm) after consecutive measurements; - Hypercalcemia (>11 mg/dL); - Hemoglobin decrease of ≥2 g/dL unrelated to treatment or other non-myeloma related symptoms; - An increase in serum creatinine of 2 mg/dL or more at the start of autonomous treatment, attributed to myeloma; - Hyperviscosity related to serum paraproteins. |

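### The lymphoma response table dates progression from baseline, not from the lowest tumour size, and has no explicit rule for a new lesion alone, so PFS is overstated in lymphoma subjects who shrink and regrow

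*Protocol*

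**What the plan says.** Appendix 14.5 sets the response categories for B-cell and T-cell lymphoma. Its size row is labelled "Change from baseline" (per cent), and that label covers every column. The PD entry is "The sum of the longest diameters of target lesions increases by >20" per cent. The SD entry is "The sum of the longest diameters of target lesions decreases by <10% or increases by ≤20" per cent. In the new-lesion row, CR, PR, MR and SD each require that there be none; PD reads "With or without new lesions". The note under the table gives "Note: ORR =CR+PR+MR; DCR= CR+PR+MR+SD".

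Two other places in the protocol treat progression differently:

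- Section 4.2, defining relapsed lymphoma: "Disease progression is indicated by the appearance of any new lesions or an increase in the diameter of existing lesions by ≥ 50" per cent.
- Appendix 14.4, myeloma PD, lists new lesions and describes lesion growth as "increasing by ≥50% from the lowest value".

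Section 10.6 runs PFS to the first recorded PD or death and otherwise censors at the last tumour measurement. Section 7.5 describes DCR as "the proportion of patients whose tumors have either decreased or stabilized for a certain period".

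**The concern.** PD is the event that ends PFS, so the table fixes the PFS date for every lymphoma subject who progresses before death. Two features of it look wrong.

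1. With baseline as the only reference, a tumour that has shrunk must regrow through all the lost ground and a further 20% before PD is reached. The better the response, the later the event.
2. A new lesion is neither required nor sufficient for PD, yet it bars every other category. A subject with a new lesion and target lesions at or below +20% has no assigned response and no explicit PFS event.

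The first makes PFS too long in responders. The second leaves the event to each assessor's inference.

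**Working it through.** The plan states no figure on this point, so there is none to reproduce. The check applies the table literally. Baseline sum of longest diameters is set to 100.

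**Inputs from the protocol.** PD above +20%, referred to baseline (Appendix 14.5); PFS to first recorded PD or death (Section 10.6); imaging every 2 cycles of 21 days in the extension phase, 2 × 21 = 42 days (general flowchart notes); lymphoma DCR = CR + PR + MR + SD (Section 7.5 and Appendix 14.5).

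**Step 1: reference point.** Baseline rule: PD above 1.2 × 100 = 120. Lowest-value rule: PD above 1.2 × n, where n is the lowest sum so far, baseline included. Growth over n needed under the baseline rule is 120/n − 1. The last column is the category the size row gives, without new lesions and with a positive PET, when the sum stands at 1.2 × n.

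| Lowest value n | PD from lowest value | PD as written | Growth over n needed as written | Table category at 1.2 × n |
|---|---|---|---|---|
| 90 | above 108 | above 120 | 33% | SD |
| 70 | above 84 | above 120 | 71% | MR |
| 50 | above 60 | above 120 | 140% | PR |
| 40 | above 48 | above 120 | 200% (120/40 = 3.0) | PR |

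Since n can never exceed 100, 1.2 × n never exceeds 120. PD as written is therefore never earlier, only the same or later. As a check, all 729 three-visit paths over nine size changes (−60, −40, −20, −5, 0, +15, +25, +60 and +140%), without new lesions, were run under both rules. The time of PD differed in 172 and was never earlier under the baseline rule. These are counts of possible paths, not frequencies expected in patients.

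**Step 2: illustration in time, under assumed regrowth.** With growth g per 42-day interval, the extra time to reach 120 instead of 1.2 × n is ln(100/n) / ln(1 + g) intervals. The range g = 10% to 30% is an assumption.

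- n = 90: 0.105/0.0953 = 1.1 down to 0.105/0.262 = 0.4 intervals.
- n = 70: 0.357/0.0953 = 3.7 down to 0.357/0.262 = 1.4 intervals.
- n = 50: 0.693/0.0953 = 7.3 down to 0.693/0.262 = 2.6 intervals.

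In practice the call falls on a scan date, so the actual delay is a whole number of intervals.

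**Step 3: new lesions.** The table applied literally, with a positive PET:

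| Target change | No new lesion | New lesion |
|---|---|---|
| −40% | PR | no category |
| −20% | MR | no category |
| −5%, 0%, +15% | SD | no category |
| +25% | PD | PD |

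**Step 4: DCR.** At the first assessment the lowest value is baseline, so the two rules agree. Any later fall below baseline has already earned SD or better as best response. Best-response DCR differed in 0 of the 729 paths. A subject with a new lesion and stable targets is excluded from SD and so, by the table, is not in the DCR numerator. DCR moves only through handling. Assume 10 lymphoma subjects, 5 with disease control and 1 unclassifiable: 5/10 = 50% if counted as not controlled, 5/9 = 56% if dropped, 6/10 = 60% if recorded as SD. With 20 subjects, 10 controlled and 1 unclassifiable: 10/20 = 50%, 10/19 = 53%, 11/20 = 55%.

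**The case against.** The strongest defence has four parts.

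- **The new-lesion gap is a literal reading.** PD is the only column that admits a new lesion, so an assessor would reach PD by elimination, and Section 4.2 shows that the authors regard any new lesion as lymphoma progression. This has force. It is too strong to say that such subjects can never have an event date. What stands is that the response table does not state the rule, and Section 4.2 is written for eligibility.
- **The table summarises a cited international standard** whose fuller rules may sit behind the row label. That cannot be checked from the protocol, and the protocol prints its own table as the criteria to use. Neither the citation nor elimination supplies a lowest-value reference.
- **The comparators serve other purposes.** Section 4.2 defines relapse with a 50% threshold, and Appendix 14.4 concerns another disease. This is fair: they show inconsistency within the protocol but do not by themselves prove the lymphoma rule wrong. Step 1 does not depend on them.
- **Efficacy is a secondary, preliminary and descriptive aim** in 21 to 42 subjects across several diseases. True. DLT and MTD are untouched, and only lymphoma subjects are affected.

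A reader might also infer that the table keeps progressing subjects on drug. The documents do not support that. Withdrawal under Section 4.6 rests on evidence of progression and is not tied to Appendix 14.5, and the synopsis stops subjects who have not reached PR after 6 cycles.

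**Conclusion.** The point stands for PFS. As written, Appendix 14.5 dates lymphoma progression late after any shrinkage: for a subject at 40% of baseline the threshold is 120 instead of 48. It also gives no explicit event rule for a new lesion with target change of +20% or less. The baseline-reference error can only lengthen PFS.

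The size of the bias in this trial cannot be computed. The protocol does not say how many lymphoma subjects will enter, respond or regrow, and the intervals in Step 2 rest on assumed growth rates. An estimate in months would need the same kind of assumption.

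A reader might infer that DCR is also too favourable. It does not follow. PD is not a component of DCR, the baseline reference leaves best-response DCR unchanged, and a new lesion excludes SD. DCR rises only if unclassifiable subjects are recorded as SD against the table or dropped from the denominator, and the protocol prescribes neither. The undefined duration of stability in Section 7.5 is the only other route by which the reference point could matter to DCR.

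**What to change.** In Appendix 14.5, state that for the PFS endpoint lymphoma PD is a >20% increase in the sum of longest diameters from the lowest on-study value (baseline included), or any new lesion. The response categories can still be measured from baseline.

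Appendix 14.5 and Section 4.2 give different accounts of lymphoma progression. They must be reconciled wherever progression governs continuing or stopping treatment; no treatment rule is proposed here.

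The cost is a short change to the appendix. No extra scans are needed, because the sums are already measured at each assessment. Lymphoma PFS may look slightly shorter.

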## Efficacy Evaluation Criteria for B-cell Acute Leukemia and T-cell Acute Leukemia

**Guidelines for the Diagnosis and Treatment of Adult Acute Lymphoblastic Leukemia in China (2016 Edition)**

1. **Bone Marrow and Peripheral Blood Efficacy Criteria**
2. CR: 1) No blasts in peripheral blood and no extramedullary leukemia; 2) Restoration of trilineage hematopoiesis in bone marrow, with blasts < 5%; 3) Peripheral blood ANC > 1.0 × 10^9/L; 4) Peripheral blood PLT > 100 × 10^9/L; 5) No relapse within 4 weeks.
3. CR with incomplete blood count recovery (CRi): PLT < 100 × 10^9/L and/or ANC < 1.0 × 10^9/L. All other criteria must meet those for CR.
4. a) Objective response rate (ORR) = CR + CRi. This disease does not conduct DCR analysis.
5. Refractory disease: Failure to achieve CR after the completion of induction therapy.
6. Progressive disease (PD): An increase of 25% in the absolute number of blasts in peripheral blood or bone marrow, or the emergence of extramedullary disease.
7. Disease relapse: In patients who have achieved CR, the reappearance of blasts in peripheral blood or bone marrow (proportion > 5%) or the emergence of extramedullary disease.
8. **Treatment Response for CNS Disease**
9. CNS Remission: Patients with CNS-2 or CNS-3 status achieve CNS-1 status.
10. CNS Relapse: The emergence of CNS-3 status or clinical symptoms of CNSL (such as facial nerve paralysis, brain/eye involvement, or manifestations of hypothalamic syndrome).

**Ⅲ Treatment Response for Mediastinal Disease**

The assessment of efficacy for mediastinal disease relies on chest CT and PET-CT. Complete Response (CR): Complete disappearance of mediastinal enlargement on CT or a negative PET. Partial Response (PR): A reduction of more than 50% in the product of the maximum vertical diameter of the enlarged mediastinum (Sum of the Products of Diameters, SPD). Progressive Disease (PD): An increase of more than 25% in SPD. Stable Disease (SD): Fails to meet the criteria for partial response or progressive disease. Relapse: Patients who achieved CR and subsequently exhibit mediastinal enlargement again.

## Contraception

**（1） Definition of women of childbearing potential and contraceptive requirements for female subjects (and their male partners)**

Women who have not undergone surgical sterilization (i.e., have not had bilateral tubal ligation, bilateral oophorectomy, or total hysterectomy) and non-menopausal women are considered women of childbearing potential. Menopause is defined as the cessation of menstruation for ≥12 months without any other medical reasons.

Female subjects of childbearing potential must have a negative blood pregnancy test at screening. From the first administration of the drug until six months after the last dose, female subjects of childbearing potential must agree to take one of the following actions:

1. Complete abstinence. The use of periodic abstinence methods (such as the calendar method, ovulation method, symptoms-temperature method, or post-ovulation method) is not permitted.
2. In addition to the correct use of condoms by male partners, the following contraceptive methods may be used:

- Intrauterine device (IUD) with a failure rate of <1% per year
- Cervical cap or diaphragm with spermicide
- Tubal sterilization
- Male partner undergoing vasectomy
- Hormonal contraceptives
- Levonorgestrel implants
- Injectable progesterone
- Oral contraceptives (combined or progestin-only)
- Vaginal contraceptive ring
- Transdermal contraceptive patch

**（2） Contraceptive requirements for male subjects (and their female partners)**

All male subjects must agree to consistently use condoms correctly from the first administration of the drug until 3 months after the last dose. In addition to correct condom use, the female partners of male subjects of childbearing potential may also choose one of the aforementioned contraceptive methods.

**（3）Procedures to be followed in the event of pregnancy**

If a subject (or their partner) becomes unexpectedly pregnant during the trial or within six months after the last dose, they must inform the investigator of the pregnancy.

## WHO Bleeding Severity Grading (Revised Version)

| Grading | Bleeding characteristics |
| --- | --- |
| Grade 1 | 1. Localized: 1-2 independent ecchymoses/petechiae, or scattered/non-confluent. 2. Oral or nasal bleeding < 30 minutes. |
| Grade 2 | 1. Melena, hematemesis, hemoptysis, fresh blood in stool, musculoskeletal or soft tissue bleeding, with bleeding < 24 hours and no need for red blood cell transfusion, hemodynamically stable. 2. Skeletal or soft tissue bleeding. 3. Significant oral or nasal bleeding lasting > 30 minutes. 4. Oral vesicles with bleeding or symptoms of significant discomfort. 5. Multiple bruises, each > 2 cm, or one bruise > 10 cm. 6. Diffuse ecchymoses/petechiae. 7. Gross hematuria. 8. Abnormal bleeding from invasive or surgical sites. 9. Unexpected vaginal bleeding, with bleeding < 24 hours and blood soaking > 2 pads. 10. Visible hemorrhage in body cavities. 11. Retinal bleeding, but vision is not affected. |
| Grade 3 | 1. Bleeding<24 hours require red blood cell transfusion as a targeted treatment measure, with hemodynamic stability. 2. Severe hemorrhage in body cavities. 3. Computed tomography (CT) shows cerebral hemorrhage, but without neurological symptoms or signs. |
| Grade 4 | 1. Bleeding resulting in weakness, including retinal bleeding leading to vision impairment. * 2. Non-fatal cerebral hemorrhage with neurological symptoms and signs. 3. Hemodynamic instability due to bleeding (hypotension, decrease in systolic or diastolic blood pressure>30 mm Hg). 4. Fatal bleeding from any site. |

* Definition of visual impairment: Visual field defects; patients suspected of visual impairment require an ophthalmological consultation

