## Definition of DLT

Any drug-related toxicity occurring within 25 days after the first dose of the investigational drug, as defined by CTCAE version 5.0, that is considered related to the investigational drug (including definitely related, probably related, or possibly related) will be regarded as a DLT:

1. Hematologic Toxicity

- Grade 3 febrile neutropenia, defined as an absolute neutrophil count (ANC) < 1.0 × 10^9^/L accompanied by fever, with a temperature > 38.3℃, or a temperature sustained ≥ 38.0℃ for more than 1 hour;
- Grade 4 neutropenia without fever lasting ≥ 5 days;
- Grade 3 thrombocytopenia (25×10^9^/L < platelet count≤50×10^9^/L) accompanied by bleeding of Grade 2 or higher according to the WHO bleeding classification (2017 revised version), or Grade 4 thrombocytopenia lasting≥7 days with platelet transfusion treatment occurring≥2 times (excluding acute leukemia patients).

1. Any Grade 3 or higher non-hematologic toxicity, including but not limited to:

- Grade 3 or higher QT interval prolongation;
- Hepatic toxicity: If the baseline levels of ALT, AST, or TBIL for the subject are ≤ Grade 1, then drug-related Grade 3 toxicity will be considered as DLT.

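### Appendix 14.8 caps some bleeding items at under 24 hours with no grade above the cap, so a longer stable bleed can lose the WHO grade that a DLT criterion needs

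*Protocol*

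**What the plan says.** Section 3.4 (Definition of DLT), with matching text in the synopsis, counts Grade 3 thrombocytopenia (platelets above 25 and up to 50 × 10^9/L) as a DLT when it is "accompanied by bleeding of Grade 2 or higher according to the WHO bleeding classification (2017 revised version"). The protocol reproduces that scale in Appendix 14.8.

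The items that matter there are:

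- **Grade 1:** skin findings, and "Oral or nasal bleeding < 30 minutes". It has no gastrointestinal or pulmonary item.
- **Grade 2, item 1** (melena or fresh blood in the stool, vomited blood, coughed-up blood, musculoskeletal or soft tissue bleeding): "with bleeding < 24 hours and no need for red blood cell transfusion, hemodynamically stable".
- **Grade 2, item 9** (unexpected vaginal bleeding): also limited to under 24 hours.
- **Grade 2, item 3:** "Significant oral or nasal bleeding lasting > 30 minutes".
- **Grade 3, item 1:** "Bleeding<24 hours require red blood cell transfusion as a targeted treatment measure, with hemodynamic stability".
- **Grade 4:** no time limit. It needs "Bleeding resulting in weakness, including retinal bleeding leading to vision impairment", symptomatic cerebral hemorrhage, "Hemodynamic instability due to bleeding (hypotension, decrease in systolic or diastolic blood pressure>30 mm Hg"), or death from bleeding.

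The DLT count drives Table 8 in Section 3.2.4: no DLT in three subjects leads to the next dose, one in three leads to expansion, one in six leads to the next dose, and two or more leads back to the previous dose.

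**The concern.** A severity scale should not rank a longer bleed below a shorter one that is otherwise the same. Here the longer bleed drops off the scale. Because Section 3.4 uses the WHO grade as a condition, the gap reaches DLT classification and so the MTD, which is a primary objective.

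The same table handles time sensibly elsewhere. Oral or nasal bleeding is Grade 1 under 30 minutes and Grade 2 above 30 minutes, so that cap has a higher grade above it. The 24-hour cap has none. The contrast points to an error in an operative rule rather than a deliberate choice.

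The setting is foreseeable: Section 8.3.1 lists thrombocytopenia and hemorrhage among anticipated events, and Section 8.4 names severe gastrointestinal or pulmonary bleeding as something to prevent.

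**Working it through.** The protocol states no figure on this point, so the check is to apply the grading rules as written to every combination.

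**Step 1: grade a drug-related gastrointestinal or pulmonary bleed that is neither debilitating nor fatal.** Inputs are Grade 2 item 1, Grade 3 item 1 and the Grade 4 instability item of Appendix 14.8.

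| Duration | Red cell transfusion | Hemodynamics | Grade as written |
| --- | --- | --- | --- |
| < 24 h | no | stable | 2 |
| < 24 h | yes | stable | 3 |
| ≥ 24 h | no | stable | none |
| ≥ 24 h | yes | stable | none |
| any | either | unstable | 4 |

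Two cells are empty, both at 24 hours or more with stable hemodynamics. A stable vaginal bleed of 24 hours or more is ungraded in the same way. Musculoskeletal or soft tissue bleeding escapes the gap because Grade 2 item 2 covers it without a time limit. The body-cavity items also have no limit, but the table lists gastrointestinal and pulmonary bleeding separately, so I do not read them as filling the gap.

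**Step 2: apply the DLT criterion at a platelet count of 35 × 10^9/L (Grade 3).**

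- Melena for 12 h, untransfused, stable: WHO Grade 2, criterion met.
- Melena for 36 h, untransfused, stable: no WHO grade, criterion not met.
- Melena for 36 h, transfused, stable: no WHO grade, criterion not met.

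**Step 3: look for another DLT route in Section 3.4.**

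- A non-hematologic toxicity of Grade 3 or higher catches the bleed only if it is itself CTCAE Grade 3 or higher.
- The item for other significant medical events is discretionary and needs discussion with the sponsor.
- Interruption of more than 14 days depends on slow recovery.

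The transfused case may well be caught by the first route. None of the three automatically catches the stable, untransfused 36-hour bleed.

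**Step 4: direction of the effect.** Under Table 8 one uncounted DLT turns 1/3 into 0/3 (next dose instead of expansion), 2/3 into 1/3 (expansion instead of stepping down) or 2/6 into 1/6 (next dose instead of stepping down). No change of this kind makes the decision more cautious. In general, with p the probability that a subject is counted as having a DLT and q = 1 − p,

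P(escalate) = q³ + 3(1 − q)q² × q³ = q³ + 3q⁵ − 3q⁶.

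Its derivative in q is 3q²(1 + 5q² − 6q³). The bracket is 1 at q = 0, rises and then falls to 0 at q = 1, so it is not negative between them. Lowering the counted rate therefore always raises the chance of escalating.

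**The case against.** The strongest reply is about when a bleed is graded. No text says that grading waits for the final duration or that a grade once met is withdrawn. A 36-hour bleed is, at hour 12, a bleed of under 24 hours and would be Grade 2 at that moment. This stands as a limit: the gap bites when the event is graded by its full duration. The protocol does not say which reading applies, so the criterion depends on an unstated convention.

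The affected cell is also narrow. It needs platelets in the Grade 3 range, a drug-related gastrointestinal, pulmonary or vaginal bleed of 24 hours or more, stable and non-debilitating, and not caught elsewhere. Grade 4 thrombocytopenia has its own criterion, which does not use the WHO grade. Table 10 describes Grade 3 as severe or medically significant, or warranting admission, and some day-long bleeds would reach that. All of this stands and limits the reach of the point without closing the gap.

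The text is visibly translated, and the 24-hour phrase may be a garbled time window for transfusion. Investigators could consult the named classification directly. That is possible, but the documents do not show it, and the appendix is the scale the protocol supplies.

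A reader might infer that every such bleed is missed. The documents do not support that, given the other DLT routes and the open question of timing. A reader might also put a number on the bias: with an assumed true DLT rate of 33% and 30% of DLTs uncounted, the formula above moves from 0.434 to 0.641. Neither input is in the protocol, and the calculation supposes that no other route catches any of these bleeds. The dark red stools seen in dogs (Section 1.4.2.4) are reported without duration and do not supply the missing share.

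**Conclusion.** The point holds in a limited form. As written, Appendix 14.8 gives no grade to a stable, non-debilitating gastrointestinal, pulmonary or vaginal bleed of 24 hours or more, although the same bleed under 24 hours is Grade 2, or Grade 3 if transfused. With Grade 3 thrombocytopenia, the longer bleed then fails the WHO condition of the DLT criterion that the shorter bleed meets. It counts as a DLT only if one of the other routes applies.

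The conclusion rests on the plain text and on grading by full duration. The direction of any resulting error is certain: escalation and the MTD can only move up. Its size cannot be derived from the documents and may be small. It still deserves correction, because the rule feeds the primary objective.

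**What to change.** Reconcile Appendix 14.8 with the cited WHO classification (2017 revision) and with the DLT criterion in Section 3.4 and the synopsis, so that a longer bleed cannot lose the grade the same shorter bleed would receive. The grade boundaries should come from that source; this review does not propose them. Not every time limit has to go, since the 30-minute limit for oral and nasal bleeding works. Then re-check the WHO grade and DLT status of bleeds already recorded.

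The cost is amended appendix wording and the re-check of recorded bleeds, with no added procedures for subjects.
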